##### Immune status

An immune status including numbers and proportions of lymphocytes, T-cells (CD3^+^), NK-cells (CD3^−^CD56^+^) and B-cells (CD3^−^CD19^+^) will be assessed at T_0_ and T_3_. Furthermore, the T-cells subpopulations cytotoxic T-cells (CD3^+^CD8^+^), T-helper cells (CD3^+^CD4^+^), TH-17 cells (CD3^+^CD4^+^CD161^+^CCR6^+^), naïve T-cells (CD4^+^CD45RA^+^) as well as memory T-cells (CD4^+^CD45RO^+^) will be identified. Additionally, numbers of T_regs_ (CD3^+^CD4^+^CD25^+^ and CD127^dim^) will be assessed. Numbers and proportions will be determined by using flow cytometry. Gating strategies will be applied as reported by Zimmer et al. and Wenning et al. [35, 36].

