### Statistics

An intention-to-treat analysis will be conducted. However, data will also be analyzed per protocol. In order to determine potential between-subjects factor effects (HIIT vs ST) at T_3_ on primary and secondary outcomes, separate univariate ANCOVAs will be used. The effects of between-subjects factor acute exercise-intervention (HIIT vs. ST), within-subjects factor measurement time-point (T1 vs. T2) and their interaction on soluble factors will be investigated with 2 × 2 mixed ANCOVAs. Covariation of participants’ levels of soluble factors at T_0_ will be considered. Post hoc Bonferroni corrected pairwise comparisons will be conducted in case of significant main effect of within-subjects factor measurement time-point. To determine if groups differ at T_1_ and/or at T_2_ simple effects analyses will be performed. ANCOVA assumptions will be explored. As measure of effect size Eta-square and Cohen’s d values, respectively, will be calculated. Finally, bivariate correlation analyses will be conducted to determine potential associations between changes in biomarkers (immune status/soluble factors) and cardiorespiratory fitness/cognitive performance/patient-reported outcomes from T_0_ to T_3_.

Statistical analyses will be performed by a statistician blinded to treatment groups coded as 1 or 2. Statistical analyses will be conducted using SPSS 25® (IBM®, Armonk, NY, USA). A result will be considered significant at *p*-value equal to or less than .05.

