## Discussion

This study will provide new information on whether the immune-modifying anti-inflammatory effects of exercise, which have previously been described in other populations, occur in persons with MS. We will combine different methods (Flow cytometry, ELISA) and markers (Immune cell subsets, cytokines and Tryptophan metabolites), instead of assessing only a few soluble factors. This will enable us to identify or verify potential mechanism of exercise-induced changes in immune function which are so far only hypothetical, but which are potentially very relevant for people with MS.

Furthermore, the implemented measurement time points, immediately before and after the first exercise session, will extend knowledge of acute exercise-induced effects on immune signalling, according to the intervention (HIIT vs. ST). Examining both acute and chronic effects of exercise within one sample constitutes a robust methodological approach, which allows investigation of any interaction between short- and long-term alterations in the immune functions.

Recent studies have shown that regular physical activity has positive effects on motor and cognitive function in persons with MS [1]. However, the potential mechanisms of exercise induced changes in immune function remain theoretical constructs as no evidence is available that the achieved improvements will impact the everyday life of the person. Here, the additional evaluation of individual activities of daily living and the required motor and process skills (AMPS [41]) will provide new insights about the potential predictors (biomarkers) that strongly impact persons related quality of life. Further the influence of varying exercise intensities will provide more detailed recommendations for rehabilitative training programs.

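### Change-score correlations between biomarkers and outcomes (about 200 to 380 pairs on the listed measures) are each judged at .05 with no term for arm or baseline, and AMPS is left out

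*Protocol article*

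**What the plan says.** The last analysis in the Statistics section is that "bivariate correlation analyses will be conducted to determine potential associations between changes in biomarkers (immune status/soluble factors) and cardiorespiratory fitness/cognitive performance/patient-reported outcomes". The changes in question span the training period, T0 to T3. No covariate is named and no pairs are singled out. The section does not say whether the two arms are pooled.

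The same section sets one rule for everything: "A result will be considered significant at" a p-value of .05 or below. Its only multiplicity correction is for time points in the acute analysis: "Post hoc Bonferroni corrected pairwise comparisons will be conducted in case of significant main effect of within-subjects factor measurement time-point".

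The Secondary outcomes section says that cognitive and functional capacity data are gathered partly to look for links with biomarker changes. The Discussion adds that "the additional evaluation of individual activities of daily living and the required motor and process skills" (AMPS) should give insight into biomarkers as possible predictors. The list of outcomes to be correlated covers only fitness, cognition and patient-reported outcomes.

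**The concern.** Three things are fixed in a way that will make the associations hard to interpret.

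- **Chance.** Many pairs are tested against one unadjusted threshold, so a sizeable number will pass it with no association behind them.
- **Arm.** A bivariate correlation over both arms mixes the link within participants with the difference between arms. If HIIT moves both a biomarker and an outcome more than ST does, the two changes correlate even when they are unrelated within each arm. The T3 comparisons use ANCOVA; the correlations have no such adjustment.
- **AMPS.** The article connects AMPS with the biomarkers, but no listed analysis does so. AMPS is scored by trained occupational therapists (Activities of daily living section), so it is not patient-reported, and it is neither a fitness nor a cognitive test.

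At stake is how far a reader can trust any reported biomarker link. The randomised comparison on regulatory T-cells is not at stake.

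**Working it through.** **Sample size (Sample size calculation section).** With d = 0.5, two-sided 5% (sidedness assumed) and 80% power, a t-test needs 64 per group. The factor for baseline adjustment is 1 − 0.7² = 0.51, and 64 × 0.51 = 32.64, so 33 per group and 66 in total. The article's figure is reproduced, and N = 66 is used below. The section labels the follow-up behind ρ = .7 as T1; I take it to mean the correlation of T0 with T3. The article gives no count or error rate for the correlations.

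**Number of pairs.**

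- Cell populations: the Immune status section begins "An immune status including numbers and proportions of lymphocytes, T-cells" and goes on to NK- and B-cells (4 populations). It then adds "Furthermore, the T-cells subpopulations cytotoxic T-cells", helper, Th17, naïve and memory cells (5 more). Regulatory T-cells make 10. One measure each gives 10; numbers and proportions give 20.
- Soluble factors: 10 by ELISA plus KYNA and QUIN = 12.
- Biomarkers: 10 + 12 = 22, up to 20 + 12 = 32.
- Outcomes, low count: VO2peak 1, cognition 4, FSMC 1, HADS 2, PROMIS 1 = 9. High count: FSMC 3 and PROMIS 2 instead = 12.
- Pairs: 22 × 9 = 198, up to 32 × 12 = 384.

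**Chance findings if nothing is associated.**

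- Expected number: 198 × .05 = 9.9, up to 384 × .05 = 19.2.
- Probability of at least one: above .999 if the tests are independent. In simulation with correlations of 0.5 within the biomarkers and within the outcomes, it is still about .97 (198 pairs) or higher.
- Such correlation leaves the average almost unchanged but widens the spread. At 0.5, the 5th to 95th percentiles are 1 to 28 for 198 pairs and 3 to 53 for 384.
- At N = 66 a correlation is significant once |r| reaches about 0.24.

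**Correlation through arm, if arms are pooled 1:1.** Suppose two changes are unrelated within arm and are shifted by d1 and d2 within-arm SDs. The pooled correlation is

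r = (d1·d2/4) / √[(1 + d1²/4)(1 + d2²/4)].

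At ρ = .7 the SD of a change score is √(2 × 0.3) = 0.775 baseline SDs, so d = 0.5 on the original scale is 0.5/0.775 = 0.645 on the change scale. Flag rates are simulated with 33 per arm.

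| Shift in both changes (SD) | Induced r | Flagged at .05 |
|---|---|---|
| 0.5 | 0.0625/1.0625 = 0.06 | 7.5% |
| 0.645 | 0.104/1.104 = 0.09 | 11.5% (about 12% by Fisher z) |
| 0.8 | 0.16/1.16 = 0.14 | 20% |
| 1.0 | 0.25/1.25 = 0.20 | 37% |

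If arm shifts only one of the two, the rate stays near 5%. Adjusting for arm brings it back to 4.9–5.2% at every shift tried, but does not lower the chance count.

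**Baseline.** If two baselines correlate at c and the follow-up deviations are independent, the changes correlate at c(1 − ρ)²/[2(1 − ρ)] = 0.15c. For c = 0.2 to 0.5 this is 0.03 to 0.075.

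**If arms are analysed separately.** The correlation through arm disappears, but the tests double to 396–768 at 33 per arm, with 19.8 to 38.4 expected by chance.

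**The case against.** The correlations come last, are worded as a search for possible associations, and sit behind a single primary outcome that alone drives the sample size. An article often leaves multiplicity for such analyses to a fuller plan. That stands as a limit on the weight of the point. It does not remove it, because the article itself fixes the method and a threshold covering every result.

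Three stronger readings are tempting and are not supported.

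- A reader might infer that the arm contrast produces many of the significant links. Pooling is not stated, and inflation needs both changes to shift. The planned d = .5 is for regulatory T-cell proportion only; the article gives no effect size for fitness, cognition or patient-reported outcomes. A 1 SD shift in both changes has no basis in it.
- A reader might infer that baseline measurement error creates spurious links. Independent error in two instruments weakens a correlation between their changes; it does not create one. Correlated baselines add little, as calculated.
- A reader might take the correlations as the trial's evidence on mechanism, because the Discussion says "This will enable us to identify or verify potential mechanism of exercise-induced changes in immune function". That sentence refers to combining assay methods and marker types. Exercise effects on immune markers are tested by the randomised ANCOVAs, whereas the correlations ask how biomarkers relate to other outcomes.

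On AMPS, the phrase on functional capacity in the Secondary outcomes section could be read to include it, which would make the Statistics list merely incomplete. The list still needs completing.

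**Conclusion.** The point holds, with chance as the main problem and arm as a secondary one. Followed as written, the plan would label about 10 to 19 of some 200 to 380 correlations significant even if no association existed. The range reflects whether each cell population counts once or twice, and the assumed number of FSMC and PROMIS scores. Correlation through arm is conditional on pooling. At the planned effect it raises the flag rate of affected pairs from 5% to about 7.5–12%, and it becomes large only as both shifts approach 1 SD. Baseline effects are small. The omission of AMPS is a real mismatch between stated aim and listed analysis. The primary ANCOVA is untouched, so this should be corrected but does not threaten the main result.

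**What to change.** 1. Replace the bivariate correlations with partial correlations, or with regression of the T3 outcome on the T3 biomarker, adjusted for arm and for both T0 values. This also settles whether the arms are pooled.
2. Add the AMPS motor and process scores to the outcome list. The family then becomes 22 × 11 = 242 to 32 × 14 = 448 pairs, with 12.1 to 22.4 expected by chance at an unadjusted .05, so the next step matters more.
3. Choose one of two treatments of multiplicity and state it: control the false-discovery rate across the correlation family, or report the associations as exploratory estimates with confidence intervals and exempt them from the .05 rule. Either is acceptable.

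The cost is a change of wording in the analysis section, using data already to be collected. The downside is fewer nominally significant associations.

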## Discussion

This study will provide new information on whether the immune-modifying anti-inflammatory effects of exercise, which have previously been described in other populations, occur in persons with MS. We will combine different methods (Flow cytometry, ELISA) and markers (Immune cell subsets, cytokines and Tryptophan metabolites), instead of assessing only a few soluble factors. This will enable us to identify or verify potential mechanism of exercise-induced changes in immune function which are so far only hypothetical, but which are potentially very relevant for people with MS.

Furthermore, the implemented measurement time points, immediately before and after the first exercise session, will extend knowledge of acute exercise-induced effects on immune signalling, according to the intervention (HIIT vs. ST). Examining both acute and chronic effects of exercise within one sample constitutes a robust methodological approach, which allows investigation of any interaction between short- and long-term alterations in the immune functions.

Recent studies have shown that regular physical activity has positive effects on motor and cognitive function in persons with MS [1]. However, the potential mechanisms of exercise induced changes in immune function remain theoretical constructs as no evidence is available that the achieved improvements will impact the everyday life of the person. Here, the additional evaluation of individual activities of daily living and the required motor and process skills (AMPS [41]) will provide new insights about the potential predictors (biomarkers) that strongly impact persons related quality of life. Further the influence of varying exercise intensities will provide more detailed recommendations for rehabilitative training programs.

## Abbreviations

ADL: Activities of daily living
AMPS: Assessment of Motor and Processing Skills
ANCOVA: Analysis of Covariance
BBB: Blood brain barrier
BICAMS: Brief International Cognitive Assessment for Multiple Sclerosis
BVMT-R: Brief Visuospatial Memory Test revised
CPET: Cardiopulmonary exercise test
EDSS: Expanded disability status scale
ELISA: Enzyme-linked immunosorbent assay
FSMC: Fatigue scale of motor and cognitive functions
HADS: Hospital anxiety and depression scale
HIIT: High-intensity interval training
HR_max_: Heart rate maximum
IDO-1: Indoleamine 2,3-dioxygenase-1
IL: Interleukin
KAT: Kynurenine aminotransferase
KYN: Kynurenine
KYNA: Kynurenic acid
min: minutes
MMP: Matrix metalloproteinase
MS: Multiple sclerosis
PROMIS: Patient-Reported Outcome Measurement Information System
QUIN: Quinolinic acid
rpm: revolutions per minute
SDMT: Symbol Digit modalities test
ST: Moderate continuous training (standard therapy)
TAP: Test battery for attentional performance
TDO: Tryptophan 2,3-dioxygenase
TGF-ß: Transforming growth factor-beta
T_regs_: regulatory T-cells
TRP: Tryptophan
VLMT: Verbal learning and memory test
VO2_peak_: Peak oxygen consumption
